## Interventions

### Explanation for the choice of comparators {6b}

We break down our samples into 3 groups based on their membership status and expiration dates. Group 1 contains all individuals with active insurance and an expiration date during the intervention period. Group 2 contains all individuals with a currently expired membership and expiration date between 1 October 2022 and the end of the pre-intervention period. Group 3 contains all members with active insurance and an expiration date after the planned end date of our intervention period. We do this because expired members require different reminders and autorenewal messages than active members, and because those with a renewal date during the intervention phase receive messages around their expiration dates which individuals with renewal date outside of this time frame cannot receive. Furthermore, we expect that individuals with expired insurance may react differently than individuals with active insurance, and that those with more imminent renewal dates may respond differently than those whose renewal dates are still far away. We randomly allocate treatment within each group, clustering individuals by phone number to prevent spillovers. Group 3 is only assigned autorenewal or control, because the renewal window opens 90 days before expiration, therefore sending reminders to a group whose insurance expires in 6 months at the earliest would not be sensible.

Due to the randomization, the treatments and control within each expiration date group (1, 2, 3) arms only differ by the treatment status. Individuals in the control arms will not receive SMS prompts for renewal or autorenewal, but will otherwise receive usual communications from the NHIA which are not related to this trial. Only participants assigned to be treated in the autorenewal arm will be able to sign up for the autorenewal platform as primary users, but will be able to add other individuals (typically dependents and other family members) to their renewal plan and pay for their renewals. All other individuals will be able to access the USSD Menu of the autorenewal platform through the short-code, but will not be able to sign up for the service. Instead, they will be shown an error message informing them that this platform is still undergoing testing and may be made available at a later date (Fig. 1).

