#### Arm 1 A, 2 A, 3A

**Table Tabc:** 

Message #	8
Day of Trial	Day 1 and Day 30 of trial
Condition	Member has not opted into autorenewal
Message	Dear Firstname Lastname, NHIA offers a new option to renew your membership automatically. You can opt-in by dialling *929*20#. For more information, call NHIA call center at [name]

Once signed up, individuals in arm 1 A will receive messages 2 and 3 on the indicated days, provided that membership has not yet been renewed otherwise. The automatic renewal is triggered 30 days before the expiration date. If the expiration date is less than 30 days away or the membership is already expired, it will be triggered the day after sign-up. If no payment or further documentation is required, insurance is renewed immediately. If a payment is required, it will be debited to the MoMo account of the participant. If payment is successful, the insurance is renewed. If payment is unsuccessful, the member is informed and the renewal will be triggered in the 3 subsequent days again. After that, the member will receive a final message suggesting they attempt renewal via one of the other platforms.

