### Secondary outcomes

**Table Tabg:** 

Outcomes	Analysis Metric	Method of aggregation	Time point
Renewal by expiration date (by t_0_), renewal without coverage gap (by t_90_)	Odds ratio between treatment and control group for each arm	Proportion succeeding in renewing insurance coverage by date	End of observation period
Coverage gap	Time ratio between treatment and control group for each arm	Mean length in days/duration until renewal	End of observation period
Acceptance of autorenewal option	Odds ratio between treatment and control,	Proportion signing up for autorenewal	End of observation period
Successful renewal via autorenewal	Odds ratio between treatment and control	Proportion of autorenewal set-ups resulting in a successful renewal	End of observation period
User experience and acceptability of intervention	Agreement with questions regarding usefulness and usability of intervention	Proportion of individuals agreeing with statements	Follow-up survey Post-intervention period

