## Statistical methods

### Statistical methods for primary and secondary outcomes {20a}

Descriptive statistics for each treatment arm at baseline will summarize sociodemographic characteristics as means, percentages, or counts with standard deviations. The primary outcome will be assessed as the difference in renewal rates between each treatment and its corresponding control group, comparing the difference between those who received renewal reminders (1R, 2R) or autorenewal prompts (1A, 2 A, 3 A) against the respective control group (1C, 2 C, 3 C). Specifically, we compare 1R vs. 1 C, 1 A vs. 1 C, 2R vs. 2 C, 2 A vs. 2 C, and 3 A vs. 3C. The primary outcome is rate of successful renewals in each group. The primary endpoint is the effect size, estimated with a logistic regression of treatment status on insurance outcome, and reported as an odds ratios with significance levels (*p* values and 95% confidence intervals). To assess whether reminders resulted in less or in shorter coverage gaps, we will conduct a duration analysis, comparing time-to-renewal between the treatment arms using Kaplan–Meier curves and Weibull regressions. All effect sizes will represent an intent-to-treat (ITT) effect, as we cannot be certain if a treatment reached the intended recipient. The secondary outcomes will be assessed using descriptive statistics and logistic regressions in order to compare the likelihood of signing up for autorenewal, and the likelihood of a successful renewal occurring, conditional on having signed up for autorenewal, across the different expiration date groups. The results will be reported as absolute differences and odds ratios. We cluster-randomize individuals by phone number in order to avoid having individuals with the same phone number in different treatment arms, which could result in spill-overs. For the analysis, we use individual-level analysis for two reasons: (1) because the treatment is addressed to each individual and timed according to individuals’ expiration dates, making this an individual-level treatment, and (2) ~ 85% of phone number clusters contain only one individual, making an application of a mixed-effects model difficult, as there would be nearly as many random intercepts as there are observations. However, we do use clustered standard errors in the analysis to account for possible intra-cluster correlations.

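### The denominator of the autorenewal success outcome includes set-ups whose renewal has not yet been triggered, which biases the Group 3 comparison downward unless observation runs long enough

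*Protocol article*

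**What the plan says.** The secondary outcomes table in the protocol article (Outcomes {12}) has a row for successful renewal via autorenewal. It is aggregated as "Proportion of autorenewal set-ups resulting in a successful renewal" and read at "End of observation period". The text shown gives no date or length for that period.

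Statistical methods {20a} plans a logistic regression for "the likelihood of a successful renewal occurring, conditional on having signed up for autorenewal, across the different expiration date groups". Sign-up is the only condition.

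The description of the autorenewal treatment sets the timing: "The automatic renewal is triggered 30 days before the expiration date". For members close to or past expiry, "If the expiration date is less than 30 days away or the membership is already expired, it will be triggered the day after sign-up".

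The section on the choice of comparators {6b} defines the groups by expiry date. "Group 1 contains all individuals with active insurance and an expiration date during the intervention period". Group 2 has already expired. "Group 3 contains all members with active insurance and an expiration date after the planned end date of our intervention period".

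**The concern.** The date that defines the groups also decides whether an automatic renewal is attempted before the data are read. Group 2 set-ups are triggered the day after sign-up. Group 1 set-ups fall due within the intervention, apart from a sign-up on its last day. A Group 3 set-up falls due within the intervention only if it expires in the first 30 days after the intervention ends. Under the stated denominator, a set-up that was never attempted is scored the same as a failed payment.

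Objective 2 asks what needs adjusting before national scale-up. A low Group 3 proportion could be taken as a payment or platform problem when part of it only reflects renewals not yet due. The cross-group contrast also carries most of the weight for this outcome. The table lists an odds ratio against control, but controls cannot sign up as primary users, so that ratio is hardly workable.

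A smaller ambiguity sits beside this. The renewal window opens 90 days before expiry and the trigger comes at 30 days. A signed-up member who renews by another route in between had no automatic attempt. The name of the outcome would not count that renewal as a success, while the wording in {20a} could.

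**Working it through.** The protocol gives no figure for this outcome, so there is none to reproduce. The check is calendar arithmetic.

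**Inputs from the protocol article**
- Trigger 30 days before expiry (autorenewal treatment description).
- Intervention of 6 months, taken as L = 183 days (Abstract, Methods).
- Annual membership, with renewal possible up to 90 days early (Background {6a}).
- Group 3 expiry after the intervention ends ({6b}).

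**Assumptions**
- Group 3 expiries are uniform from day L to day H after the start. H = 365, or H = 455 if policies were renewed up to 90 days early.
- The true success rate s per due renewal is the same in every group. The main value is 0.70, with a range of 0.30 to 0.90.
- Observation runs E days past the intervention, and the platform keeps triggering renewals during that time.

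**Formulas**
- Share of Group 3 due = min(1, (E + 30)/(H − L)). H − L is 365 − 183 = 182, or 455 − 183 = 272.
- Observed Group 3 proportion = s × share due.
- Artefactual odds ratio = odds(s × share due)/odds(s), which would be 1 without the artefact.

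**Worked case, E = 0, H = 365, s = 0.70:** share due 30/182 = 0.165; observed proportion 0.165 × 0.70 = 0.115; odds 0.130 against 2.33; odds ratio 0.056.

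| E (days) | Share due, H = 365 | Group 3 observed | Odds ratio | Share due, H = 455 | Odds ratio |
|---|---|---|---|---|---|
| 0 | 16% | 11.5% | 0.06 | 11% | 0.04 |
| 30 | 33% | 23.1% | 0.13 | 22% | 0.08 |
| 90 | 66% | 46.2% | 0.37 | 44% | 0.19 |
| 120 | 82% | 57.7% | 0.58 | 55% | 0.27 |
| 150 | 99% | 69.2% | 0.96 | 66% | 0.37 |
| 180 | 100% | 70.0% | 1.00 | 77% | 0.50 |
| 270 | 100% | 70.0% | 1.00 | 100% | 1.00 |

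All of Group 3 is due once E + 30 reaches H − L. That is E = 152 days (about 5 months) for H = 365, and E = 242 days (about 8 months) for H = 455.

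**Other success rates, H = 365:** for s = 0.30, 0.50, 0.70 and 0.90 the odds ratio is 0.12, 0.09, 0.06 and 0.02 at E = 0, and 0.58, 0.49, 0.37 and 0.16 at E = 90.

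**Dates in Trial status:** the intervention ended on 31 December 2024. Counting from 20 May 2024 gives L = 225, and from 19 September 2024 gives L = 103. At E = 0 the share due is 13 to 21% for L = 225 and 9 to 11% for L = 103.

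**After the fix:** with only triggered set-ups in the denominator, equal success per due renewal gives an odds ratio of 1 whatever E is.

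**The case against.** The strongest objection concerns the time point. The outcome is read at the end of the observation period, not of the intervention, and the protocol uses these as separate terms. Its other outcomes point to a longer window. Renewal by day 90 after expiry, for Group 1 members who expire at the very end, needs about 90 further days. Measuring renewal by expiry in Group 3, as the tables imply for each arm, needs observation past the Group 3 expiries, and by then every trigger has passed. The participant timeline figure is not shown and may date the period. This protocol version is dated about ten months after the intervention ended, so a long window is plausible.

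This stands as far as size goes. A reader might infer that Group 3 success is capped at about 16% and that the calendar alone decides the comparison. The documents do not support that, because both statements require observation to stop with the intervention. The objection does not remove the point, since no text shown commits to a window long enough for every Group 3 set-up to fall due, and the outcome carries no condition that the renewal was due. The sensitivity analyses in {20b} and the Discussion concern which messages a participant received, not this denominator.

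It is also fair that the expiry groups are not randomised against each other and are expected to respond differently. Equal true success is assumed here only to isolate the artefact. Finally, the article says that the platform used is recorded for each transaction, so a renewal by another route can be identified. That leaves a wording ambiguity there, not a data gap.

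**Conclusion.** The point holds for Group 3 on this one secondary outcome. The protocol fixes both the denominator and the comparison, and together they count renewals not yet attempted as failures. The bias in the Group 3 contrast is downward. Under even expiry and 70% true success, the odds ratio where the truth is 1 runs from about 0.06 (observation ends with the intervention, the extreme case) through about 0.37 (90 days later, policies to day 365) to 1 (from about 5 months, or about 8 months with policies to day 455). The expiry distribution, the latest expiry date, the success rate and continued triggering after the intervention are all assumptions.

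A reader might extend this to the trial's effectiveness results. That does not follow: no primary comparison uses this denominator, and Groups 1 and 2 are not materially affected by the timing.

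**What to change.** Define the denominator as set-ups with at least one automatic renewal attempt triggered by the data cut, and state the date of that cut. Count success as a renewal made by the autorenewal platform. Restrict the cross-group comparison in {20a} to these set-ups. Report two further categories separately: set-ups not yet due, and set-ups renewed by another route before the trigger.

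This changes the wording of one outcome definition and one analysis sentence. Transaction date, platform used and autorenewal registration status are already in the routine extract described in {18a}, so no new data are needed. The cost is precision: if observation is short, few Group 3 set-ups remain in the denominator and its interval will be wide.

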## Participant timeline {13}

### Sample size {14}

We compute sample size estimations for a binary-outcome, parallel group superiority trial assuming 95% significance (α = 0.05), 80% power (β = 0.20), and a normal distribution [25, 26]. In order to account for the clustered randomization, we inflate the sample size estimate with the design effect coefficient [(1 + (n-1) ρ], where n is the cluster size and ρ is the intraclass correlation coefficient [27, 28]. We assume an intracluster correlation coefficient of ρ = 0.2, an average cluster size of n = 1.3 for the verified sample, and n = 1.7 for the unverified number sample based on our estimates of sample characteristics. We conservatively assume an effect size of 10% based on systematic reviews of SMS-based reminder systems in health care settings [14–19, 29, 30]. This gives us a requirement of 2530 individuals per arm. Since the phone number validation exercise showed that 48% of NHIS members did not have their current, up-to-date phone number on file, we must assume that only a fraction of SMS-reminders in the unverified population will reach the intended target, so we can expect smaller effect sizes for the unverified number sample. If unintended spill-overs occur, this could further attenuate effect size. As a result, we chose to randomly select 30,000 phone number clusters into each arm for the unverified number sample. This is the maximum sample size feasible due to budget constraints. With this sample size, an effect size as small as 3.46% would be detectable in the unverified number sample.

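### The design effect uses mean cluster sizes although clusters are unequal, so the 2,530-per-arm requirement is modestly too low for the sample whose mean it rests on

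*Protocol article*

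**What the plan says.** All of the sample size reasoning is in Sample size {14} of the protocol article.

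- The calculation is for a binary outcome, "assuming 95% significance (α = 0.05), 80% power (β = 0.20), and a normal distribution".
- For clustering, "we inflate the sample size estimate with the design effect coefficient", given there as 1 + (n − 1)ρ with n the cluster size.
- "We assume an intracluster correlation coefficient of ρ = 0.2". What the article inserts for n is a mean in both samples: "an average cluster size of n = 1.3 for the verified sample", with a larger value, 1.7, where numbers were not verified.
- On the size of effect, the text reads "We conservatively assume an effect size of 10" per cent. It does not say whether this is relative or absolute, and it gives no control renewal rate.
- "This gives us a requirement of 2530 individuals per arm". One figure is reported, without saying which of the two cluster sizes produced it.

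Elsewhere, Eligibility criteria {10} admits phone numbers registered for up to 6 members. Statistical methods {20a} plans an individual-level logistic regression with standard errors clustered by phone number, and states that about "85% of phone number clusters contain only one individual".

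**The concern.** The factor 1 + (n − 1)ρ is exact when every cluster has n members. Here a cluster is the set of people sharing a phone number, so its size is a whole number. A mean of 1.3 or 1.7 can arise only from a mixture of sizes, and the article's own remark about singletons confirms that sizes vary.

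When individuals are weighted equally and errors are clustered, larger clusters contribute more than proportionally to the variance. The relevant n is then the size-weighted mean E[m²]/E[m], which exceeds E[m] whenever sizes differ. Using the plain mean therefore always understates the design effect. At stake is the accuracy of the only stated requirement for 80% power, and so the reading of a null result in any verified arm close to that size.

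**Working it through.** **Inputs.** From Sample size {14}: α = 0.05 (two-sided assumed, as sidedness is not stated), 80% power, ρ = 0.2, means 1.3 and 1.7, effect 10%. From Eligibility criteria {10}: size at most 6. Assumed, because not given: a control rate of 40% and a relative effect, so 40% v 44%.

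**Reproducing 2,530.** Per arm without clustering:

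n = (1.960 + 0.842)² × (0.40 × 0.60 + 0.44 × 0.56) / 0.04² = 7.849 × 0.4864 / 0.0016 ≈ 2,386

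Design effect 1 + (1.3 − 1) × 0.2 = 1.06, and 2,386.1 × 1.06 = 2,529.2, which rounds up to 2,530. The match depends on the assumed control rate. With the pooled-variance form and the same factor, 30% gives 3,988, 45% gives 2,047 and 50% gives 1,659. An absolute 10-point effect gives at most about 415, so only the relative reading fits.

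**Correct factor.** With cluster sizes m, the variance of an arm's proportion is proportional to Σ m[1 + (m − 1)ρ] / (Σ m)². The design effect is therefore

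DE = 1 + (E[m²]/E[m] − 1)ρ

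**Floor at mean 1.3.** For whole numbers (m − 1)(m − 2) ≥ 0, so E[m²] ≥ 3E[m] − 2 = 1.9. Equality holds for 70% singletons and 30% pairs. Then E[m²]/E[m] ≥ 1.9/1.3 = 1.462 and DE ≥ 1.092. This uses only the article's mean and ρ.

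**If 85% of verified clusters were singletons (assumption).** The other 15% must average (1.3 − 0.85)/0.15 = 3 members.

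- All of size 3: (0.85 + 0.15 × 9)/1.3 = 1.692, DE 1.138.
- Three quarters of size 2, one quarter of size 6: (0.85 + 0.15 × 12)/1.3 = 2.038, DE 1.208.

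**Requirement and power.** Requirement = 2,530 × DE/1.06. Power at 2,530 ≈ Φ(2.802 × √(1.06/DE) − 1.960). Both depend on the ratio of design effects, so the assumed control rate hardly matters to the percentage shortfall.

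| Sizes, mean 1.3 | DE | Requirement | Increase | Power at 2,530 |
|---|---|---|---|---|
| As planned | 1.06 | 2,530 | – | 80% |
| 70% one, 30% two (floor) | 1.092 | 2,607 | 3% | 78.8% |
| 85% one, rest three | 1.138 | 2,717 | 7% | 77.1% |
| 85% one, rest two or six | 1.208 | 2,883 | 14% | 74.7% |

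Simulating clustered binary data with cluster-robust variance (4,000 runs) gave 79.0%, 77.7% and 74.6% for the last three rows.

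**If 2,530 rests on mean 1.7.** The planned factor is 1 + 0.7 × 0.2 = 1.14, and a control rate of about 41.7% then gives 2,530. The floor is E[m²] ≥ 3 × 1.7 − 2 = 3.1, so E[m²]/E[m] ≥ 1.824 and DE ≥ 1.165. That is 1.165/1.14 = 1.022, about 2% more. On this reading the unadjusted size is 2,530/1.14 ≈ 2,219, and the verified sample would need 2,219 × 1.092 ≈ 2,423 at its floor.

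**The case against.** **The basis of 2,530 is not stated.** A reader might infer that 2,530 is certainly built on 1.06 and is too low for every set of cluster sizes averaging 1.3. The article does not support that. A factor of 1.14 with a control rate near 41.7% gives the same figure, and 2,530 would then cover the verified sample at its floor and also in the all-threes case (2,219 × 1.138 ≈ 2,525). This objection stands as to certainty. Against it, the 1.06 reading needs only a round 40%, while the 1.14 reading needs an odd rate and still understates the need of its own sample.

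**The 85% share may not belong to the verified sample.** Also right. The unverified sample has 281,281 members (Eligibility criteria {10}) in 240,000 clusters (Sequence generation {16a}), a mean of 1.17. With 85% singletons the rest would average (1.172 − 0.85)/0.15 ≈ 2.1, which is more natural than exactly 3. The range of 2,720 to 2,880 is therefore conditional and should not be read as the article's own figure. The floor does not need it.

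**The effect is small and little depends on it.** At 2,530 the detectable relative effect moves from 10% to about 10.15% at the floor (10 × √(1.092/1.06)). The floor shortfall disappears if ρ is 0.13 (0.06/0.462). The verified sample takes everyone eligible from the verification exercise, and the unverified size was set by budget. Clustered standard errors mean that confidence intervals and p values already reflect unequal clusters. All of this stands and limits the weight of the point, but it does not make the stated figure right.

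**Conclusion.** The point holds in a limited form. Mean cluster sizes were put into an equal-cluster formula although the sizes must differ, so the design effect is understated for whichever sample it was computed for. On the likelier reading (mean 1.3, with 40% v 44% assumed), the requirement is at least about 2,607 and power at 2,530 is at most about 78.8%. If the 85% singleton share also held in the verified sample, it would be about 2,720 to 2,880 with power about 77% to 75%. On the other reading (mean 1.7), the shortfall is at least about 2% for that sample.

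A reader might go on to infer that verified Group 3 is underpowered because of this. The text does not show it. Explanation of design choice describes that group's size only in words, and the sample composition figure is not shown. The correction changes the status only of an arm lying between 2,530 and the corrected requirement. Most arms are far above either: 30,000 clusters each in the unverified sample, and about 7,600 people on average in the verified one (61,097/8). The planned inference is not affected. What needs correcting is the stated requirement.

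**What to change.** In Sample size {14}:

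1. State the control renewal rate, that the 10% is relative (if so), and which mean cluster size underlies 2,530.
2. Replace n by E[m²]/E[m], computed separately for the verified and unverified samples from the actual distribution of members per phone number.
3. Restate the requirement, and state which verified arms meet it.

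The cost is one tabulation of data the trial already holds, a recalculated figure and a sentence or two. No extra enrolment is needed. Trial status reports that the interventions were completed on 31 December 2024, so the gain is an accurate power statement when results from the smaller verified arms are interpreted.
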